### Aims

This study aims to (1) collect quantitative data about the level of PDAC patients engagement and their rate of understanding of the received information and (2) investigate the association between engagement and rate of understanding and of these two variables with the level of compliance.

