### Statistical Analysis

Categorical variables will be compared using Fisher or chi-square tests and continuous variables using *t* test or Mann–Whitney tests, as appropriate. Subgroups with different levels of engagement will be compared for variables such as sex, age, education, geographic area, stage of disease, type of proposed treatment, and other available data. The PHE-s® questionnaire provides continuous data. The possible correlation of the level of engagement with the clarity of the received information that will be considered as a categorical variable divided in quartiles and with the compliance with treatments will be tested by a Pearson test. Two different univariate and multivariate logistic regression analyses will be run considering patient engagement and compliance as outcome variables and patients' and disease features and the clarity of communication as explanatory variables.

The “enter” method will be employed including all variables that had resulted to be significant at the univariate analysis. Tests of statistical significance and confidence intervals will be two-sided; a *p* < 0.05 will be considered to be statistically significant. A dedicated software (Medcalc 12.1, Belgium) will be employed.

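### Multivariable models admit only univariately significant variables, with no exemption for understanding, so an adjusted estimate of the main exposure often will not exist; engagement is not named as explanatory for compliance

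*Protocol article*

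**What the plan says.** The Statistical Analysis section plans univariate and multivariate logistic regressions "considering patient engagement and compliance as outcome variables", with "patients' and disease features and the clarity of communication as explanatory variables". The multivariable models use the enter method, "including all variables that had resulted to be significant at the univariate analysis". No separate entry threshold is given. The only level in the section is p "< 0.05 will be considered to be statistically significant", and "Tests of statistical significance and confidence intervals will be two-sided", so entry at two-sided 0.05 is implied. Nothing is exempt from the screen, neither clarity nor any patient or disease feature.

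For the correlation analysis, clarity is "considered as a categorical variable divided in quartiles". The same sentence tests engagement against compliance with a Pearson test. The second aim (Aims) is to "investigate the association between engagement and rate of understanding and of these two variables with the level of compliance", and the Outcomes section names the same associations. The Power Size Calculation section expects 45 to 60 patients and gives no effect size or power.

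**The concern.** The entry rule treats the study's own exposure as one more candidate covariate. If its crude association misses p < 0.05, the model contains no adjusted estimate of it. If the crude association reaches p < 0.05, often because chance has pushed it upwards, the adjusted estimate appears. The adjusted results that reach print are therefore selected for size. Their intervals and p-values take no account of that selection.

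The rule also decides confounding control by significance in a small sample. Age, education or stage can be true confounders and still miss 0.05 in 45 to 60 patients, so the adjustment set will vary by chance.

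The second gap concerns engagement. The second aim asks how engagement relates to compliance, but the list of explanatory variables does not name engagement.

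A pilot is mainly useful for the estimates it hands to the next study. The Discussion also says that action on clinical communication will follow if the hypothesis is supported, so biased or absent adjusted estimates would matter.

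**Working it through.** **1. The plan's own figure.** The only figure to reproduce is enrolment. About 500 patients a year is 500/4 = 125 per 3 months; 45/125 = 36% and 60/125 = 48% of that inflow. This is a feasibility statement. There is no power calculation to check.

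**2. Inputs for the screen.** From the article: n = 45 or 60; two-sided 0.05; entry by univariate significance; clarity in quartiles. The quartile coding is stated for the correlation analysis, and I assume it carries over to the regressions. Not in the article, so assumed: a true odds ratio (OR) per SD of exposure of 1.5, 2.0 or 2.5, and an outcome proportion p0 at average exposure of 50% or 80%.

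**3. Method.** Draw x from a standard normal and y from logit P(y = 1) = a + ln(OR)·x, with a = ln(p0/(1 − p0)), that is 0 or 1.386. Use 4,000 data sets per scenario, setting aside the few (at most 11 per scenario) with fewer than three patients in either outcome group.
- Continuous exposure passes if |b/SE(b)| > 1.96.
- Quartile exposure passes if the 3-df likelihood-ratio statistic exceeds the 95% point of chi-square on 3 df.

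**4. Results.** The last two columns are for the continuous exposure.

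| True OR per SD | p0 | n | Passes, quartiles | Passes, continuous | Median crude OR, all studies | Median crude OR, studies that pass |
|---|---|---|---|---|---|---|
| 1.5 | 50% | 45 | 16.8% | 21.8% | 1.52 | 2.39 |
| 1.5 | 50% | 60 | 18.5% | 28.7% | 1.51 | 2.09 |
| 1.5 | 80% | 45 | 15.3% | 16.2% | 1.53 | 2.90 |
| 1.5 | 80% | 60 | 16.7% | 19.5% | 1.50 | 2.41 |
| 2.0 | 50% | 45 | 38.7% | 54.2% | 2.07 | 2.62 |
| 2.0 | 50% | 60 | 46.7% | 67.0% | 2.03 | 2.34 |
| 2.0 | 80% | 45 | 30.6% | 38.0% | 2.06 | 3.12 |
| 2.0 | 80% | 60 | 39.6% | 52.5% | 2.07 | 2.66 |

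At OR 2.5 the quartile exposure passes in 47% to 71% of studies and the continuous one in 59% to 88%. With no true effect, the quartile test passes in 6% to 9%, slightly above its nominal 5%, so its pass rates above are if anything generous.

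- At OR 2.0, quartile clarity is dropped in about 53% to 69% of studies.
- The median crude OR is close to the truth across all studies, but among studies that pass it is 2.1 to 2.9 for a true 1.5 and 2.3 to 3.1 for a true 2.0.
- The pass rates hold equally for a confounder. One whose crude association with the outcome is OR 1.5 per SD, entered as continuous, passes in 16% to 29% of studies and is left out of the rest.

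**5. Engagement and compliance.** The Aims ask for the association of both engagement and understanding with compliance. The regression sentence names engagement only as an outcome, and its explanatory list is patient features, disease features and clarity. The only analysis that explicitly links engagement with compliance is therefore the Pearson test, which adjusts for nothing.

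**6. Size of a forced compliance model.** With quartiles: 3 (clarity) + 1 (age) + 1 to 2 (education) + 1 to 3 (stage) + 1 (PHE-s) = 7 to 10 df. With understanding as a continuous rate: 1 + 1 + 1 to 2 + 1 to 3 + 1 = 5 to 8 df. If 80% were compliant, the smaller outcome group would be 0.20 × 45 = 9 or 0.20 × 60 = 12 patients.

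**The case against.** The case for the plan has real force.

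- **Unadjusted results are not filtered.** The Pearson tests and univariate regressions do not depend on significance. A reader might infer that the exposure estimate will be published only when it is large. The article does not support that; only the adjusted estimate is conditional. This objection stands and limits the point.
- **The second aim asks for association, not adjusted association.** The Pearson test supplies one for engagement and compliance. A reader might infer that this relation is never estimated, or that a formal hypothesis goes untested. Neither holds: the Hypothesis section states no effect of engagement on compliance, and only the Discussion suggests that chain. Patient features could also be read to include engagement, though the text does not say so and the screen would still apply.
- **Leaving engagement out can be right.** If engagement lies on the path, a compliance model without it targets the total association of understanding with compliance. That is a reason to report both models, not to omit one.
- **The sizes are assumed.** Effects and outcome proportions are not in the article, and the inflation was computed for the crude OR, not the adjusted one. A calculation on the correlation scale would not help: 52% (n = 45) or 65% (n = 60) at an assumed r of 0.30 is the power of a Pearson test, not the pass rate of the logistic screen.
- **It is a small pilot.** Few patients do limit the number of covariates. That argues for a short fixed list, not for choosing the list by p-value.

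**Conclusion.** The concern holds as a stated rule that gives a worse result than an equally simple alternative. Followed as written, the plan yields an adjusted estimate of understanding only when its crude association is significant. Under an assumed OR of 2.0 per SD and an outcome proportion of 50% to 80%, that happens in about 31% to 47% of studies with clarity in quartiles. Other assumed effects move the figure: 15% to 19% at OR 1.5, and 47% to 71% at OR 2.5. The direction does not depend on these choices: selection on significance favours large estimates and omits weaker true confounders.

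The conclusion also rests on reading 0.05 as the entry threshold, and on treating clarity in the regressions as the rate of understanding defined under Variables.

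The engagement gap is narrower. As written, its association with compliance has an unadjusted test and no explicitly planned adjusted one.

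A reader might conclude that the study is invalid or that the second aim is left unanswered. It is not: the unadjusted estimates remain, and the article makes no power claim. This should be corrected before analysis.

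**What to change.** Replace the entry rule in Statistical Analysis as follows:

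- Drop univariate significance as a condition for entry, and present the univariate results as descriptive.
- Keep understanding in both the engagement and the compliance model, entered as a continuous rate rather than in quartiles.
- Add the PHE-s score to a compliance model, and report the understanding–compliance estimate with and without it, because the Discussion places engagement on the path.
- Name in advance a very short covariate set chosen on subject matter, for example age, education and stage, and cut it to suit the smaller outcome group. Use a penalised fit if events are few.
- Report every estimate with its confidence interval, whatever the p-value.

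The cost is a change of wording, using variables already on the CRF. The downside is a few degrees of freedom in every model, and more if the quartile coding is kept. If few patients are non-compliant, even the continuous version of the full example set may be unstable or show separation. The fixed list may then have to shrink to one or two covariates.

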### Power Size Calculation

There have been no previous studies on the association between the patient's understanding rate and the level of engagement and the consequent level of compliance in patients with PDAC. This is, therefore, a pilot study, and power size cannot be calculated. Considering that at S. Raffaele Hospital, some 500 new PDAC patients are seen per year, with the established inclusion criteria, it is considered plausible that 45–60 patients will be enrolled in 3 months.

## Discussion

Active engagement of the patient to the therapeutic program has been shown to be an important factor not only to obtain improved compliance but also to improve the outcomes (13, 14).

Data on the communication between physicians and patients with PDAC are scanty, and patients' engagement has not been systematically evaluated in this context (15).

We hypothesize that the clarity of communication between the treating physician and the patient and the degree of comprehension by the patient, especially during the first phases of the cure, are associated with the level of engagement and consequently with the compliance of patients with PDAC.

If the present pilot study will support this initial hypothesis, further action to improve the clarity of the clinical communication will be promoted.

## Ethics Statement

The study was be performed under the Declaration of Helsinki (2013) as well as the Good Clinical Practice International Ethical and Scientific Quality Standards. The study protocol was approved by the Ethics Committee of the San Raffaele Hospital on June the 14th, 2019, n.52/INT/2019 and is published in ClinicalTrials.gov (NCT04257955). The database does not contain names or identification numbers that may compromise patient anonymity. Participation in the study was voluntary, after signed informed consent. The written informed consent was be obtained by the study collaborators. The results of the study will be disseminated among representatives of the medical community through dedicated medical conferences and published articles.
